#### Histology and flora detection

2.8.5

Samples with the same number of cases in exposed group and nonexposed group were respectively selected for testing, in strict accordance with genomics, proteomics, metabolomics, intestinal flora, and tongue coating flora detection methods for analysis. The following points should be paid attention to in the process of index detection:

1.Select patients with good compliance to ensure timely medication and keep a light diet during medication to avoid interference from alcohol and carbonated beverages.2.Determination of clinical biochemical indexes fasting for 12 hours, and within 24 hours should not be intense sports. Blood should be collected in the decubitus position, and rest in the decubitus position for 1.5 to 2 hours before blood collection. Morning urine and middle urine should be taken. Feces avoid the pollution of urine and toilet walls, collect fresh feces from the middle and rear part of the excretion, and dig up the feces from the inner side of the middle part as samples.3.Sample collection is limited to 1 month and the collected samples are transported in a centralized way. Biologic samples should be stored in a refrigerator at −80°C. Theoretically, all tested samples should be analyzed within 6 months.

#### Information collection at different time points

2.8.6

1.0th week: Collect demographic data, TCM syndromes of CHD angina pectoris, western medicine classification of CHD angina pectoris, SAQ in main curative effect and secondary curative effect, routine admission examination, genomics, proteomics, metabolomics, intestinal flora, and tongue coating flora.2.4th week: SAQ, routine admission examination, adverse events, genomics, proteomics, metabolomics, intestinal flora, and tongue coating flora were tested for primary events and secondary events.3.12th week: SAQ, routine admission examination, adverse events, genomics, proteomics, metabolomics, intestinal flora, and tongue coating flora were tested in the primary events and secondary events.4.24th week: Detect the main curative effect, death in secondary curative effect, readmission due to cardiovascular events and adverse events.5.48th week: Check the main curative effect, death in secondary curative effect, readmission due to cardiovascular events and adverse events (Table 1).

**Table 1 T1:**
[figure not shown]
Patient-related information collection process.

### Information collection methods

2.9

In 0th week, relevant patient information was collected by consulting medical records, medical record systems, or interviews. In the 4th, 12th, 24th, and 48th weeks, interviews, telephone calls, WeChat (which can establish WeChat groups for patients and be managed in a unified way), or outpatient follow-up system are conducted to record the occurrence time and data of follow-up indicators and establish a statistical database.

### Data management

2.10

#### Original data management and archiving

2.10.1

Cardboard case report form (CRF) is adopted, and all CRFs will come into effect after being reviewed and signed by researchers. All CRFs and CRF modification traces are retained. Each test report of the subject was pasted at the designated position.

#### Data entry and storage

2.10.2

The data are entered into the computer by 2 persons and 2 persons using EpiData 3.1 database, and the data are entered into the computer by 2 trained professionals, respectively. The database is established by EpiData 3.1 for data entry. According to the research content, a data entry guide will be prepared and data entry personnel will be specially trained before data entry. Data entry personnel enter data according to the entry guide.

#### Writing of data verification and answers to questions

2.10.3

The entered data will be checked one by one according to the Data Verification Plan (SAP). SAP needs the signature and approval of the data administrator and statistician.

Verification methods include systematic verification and manual medical verification. Systematic verification mainly uses SAS 9.3 software to write verification procedures and generate data clarification form (DCF). All data query contents found through manual medical verification and systematic verification will be input into the project data query database, and the data management unit will make a formal DCF. DCF shall be sent to the clinical research supervisor after being checked and found to be correct. After re-examination by the inspectors, they will be handed over to researchers in various research centers for examination and answer. Only after receiving the DCF with the signature and date of the researcher can it be confirmed that the DCF has been answered and the database can be modified. The original DCF will be stored in the special filing cabinet for the project.

Any changes to the database will be recorded, recording when, by whom, and for what reason (Fig. 3).

**Figure 3 F3:**
[figure not shown]
Data management general process. CRF = case report form.

### Statistical analysis

2.11

#### Statistical analysis of data

2.11.1

Before the statistical analysis of clinical test data, the statistical analysis personnel shall formulate a statistical analysis plan, specify detailed statistical analysis steps, and carefully check, clean up, and confirm the clinical test data. The analysis content includes case elimination and shedding analysis, checking the number of completed cases, elimination and shedding in each center, descriptive statistical analysis, listing the frequency distribution of each variable, comparison of baseline data of clinical characteristics before treatment, analysis of concomitant medication, analysis of curative effect, safety evaluation and analysis of missed visits, etc. All statistical analysis processes are programmed and archived for future reference.

#### Main statistical analysis methods

2.11.2

Descriptive analysis and inferential analysis of clinical features before and after treatment were as follows:

1.Metrologic data: Comparative analysis before and after treatment between groups or within groups. First, normal test is carried out on the distribution of variables.(a)When obeying normal distribution, statistical description is expressed by mean number, standard deviation, number of cases, minimum value and maximum value, etc. Statistical method is *t* test or variance analysis.(b)Nonnormal distribution. Statistical description is expressed by median, upper quartile (Q1), lower quartile (Q3), 95% confidence interval, etc. Statistical method is analyzed by rank sum test (Wilcoxon method).(c)If the influence of the center or other factors is considered, covariance analysis is used.2.Counting data: Descriptive statistical analysis is made by frequency table, percentage, or composition ratio. Comparative analysis before and after intra-group or intra-group treatment was performed by Chi-squared test and Fisher exact probability method. At the same time, relative risk was calculated to illustrate the correlation strength between exposure and outcome.3.Grade data: Rank sum test (Mann–Whitney method) was used for comparison between groups.4.Analysis of influencing factors of curative effect: Regression analysis is adopted, including age, sex, treatment, and other factors that may affect the judgment of curative effect.5.The incidence rate and median time of cardiovascular events were analyzed by Kaplan–Meier method, and Cox regression analysis was used to process truncated data of cardiovascular events caused by missed visits.6.Stratified analysis: Compare the stratified curative effects by drug usage and drug treatment duration. Baseline comparison test level *α* = 0.05, and efficacy comparison test level *α* = 0.05 between groups. General statistical tests adopt bilateral tests, and those with *P* <.05 are considered to have statistical significance.

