## Method

2

A prospective cohort study was conducted among patients with CHD angina pectoris who were treated with oral Chinese patent medicine and conventional western medicine. The patients were divided into exposed group and nonexposed group according to whether or not the patients with CHD angina pectoris were treated with Chinese patent medicine. The exposed group was treated with TCM combined with conventional western medicine, while the nonexposed group was treated with conventional western medicine alone. Patients need to be hospitalized for 2 weeks as the introduction period and whether to enter the group is determined according to the treatment and medication conditions of the patients. The follow-up time points were 0th, 4th, 12th, 24th, and 48th weeks. The main events, secondary events and adverse events were used as the evaluation criteria for clinical efficacy of CHD angina pectoris. In the experimental study, we will use strict indicators to detect standard operation procedure for multigroup and bacteria detection. It is hoped that the research method with higher evidential value will be adopted to compare the short-term, medium-term, and long-term effects of Chinese patent medicine combined with conventional western medicine and conventional western medicine alone in the treatment of CHD angina pectoris, so as to tap the clinical efficacy advantages of TCM and provide reliable data support for its clinical application. The technical route is shown in Figure 1.

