#### Diagnostic criteria of western medicine

2.2.1

Diagnostic criteria for CHD angina pectoris: According to the guidelines for the diagnosis of CHD angina pectoris formulated by the American Heart Association and the Heart Association (ACC/AHA) in the Guidelines for the Treatment of Chronic Stable Angina Pectoris (2007) and the Guidelines for the Management of Patients with Unstable Angina Pectoris and Non-ST-Elevation Myocardial Infarction (2011), and referring to the Guidelines for the Diagnosis and Treatment of Chronic Stable Angina Pectoris in China in 2007, and the Guidelines for the Diagnosis and Treatment of Unstable Angina Pectoris and Non-ST-Elevation Myocardial Infarction in China in 2007, diagnostic criteria are formulated by Chinese Society of Cardiology, Chinese Journal of Cardiology. And the Chinese Medicine Research Association of China and Western Medicine combined with the Cardiovascular Disease Prevention and Rehabilitation Committee established the Standard for the Consensus of Integrative Medicine for Integrative Medicine for the Treatment of Coronary Heart Disease (2019).

Diagnosis can be made by meeting any one or more of the following:

1.The definite history of old myocardial infarction.2.Coronary angiography or computed tomography angiography examination showed that the diameter of at least 1 main branch of coronary artery was ≥50%.3.Patients with ST-segment depression or T-wave inversion after coronary revascularization (percutaneous transluminal coronary intervention [PCI] or coronary artery bypass grafting [CABG]).

The diagnosis of unstable angina pectoris of CHD refers to the Guidelines for Diagnosis and Treatment of Unstable Angina Pectoris and Non-ST-Segment Elevation Myocardial Infarction issued by Chinese Society of Cardiology and Chinese Journal of Cardiology in 2007, including the following subtypes:

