### Regulations on combined use of drugs

2.6

Patients with CHD angina pectoris can be treated with the original scheme before admission during the study period, and the admission period is 2 weeks, so that the patient's condition is stable and meets the admission criteria.

During the study period, for patients with hypertension, diabetes, hyperlipidemia, and other diseases, the antihypertensive, hypoglycemic, and lipid-lowering treatment schemes before admission can be maintained. The name, dosage, and usage of the drugs are recorded in detail in the study medical records. It is forbidden to adjust the dosage and usage of β-receptor blockers, calcium ion antagonists, and other drugs that affect the curative effect of CHD angina pectoris.

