### Follow-up time point

2.7

Patients need to be hospitalized for 2 weeks as the introduction period and whether to enter the group is determined according to the treatment and medication conditions of the patients. The follow-up time points were 0th, 4th, 12th, 24th, and 48th weeks. The main curative effect, secondary curative effect, and concomitant medication changes of patients were observed.

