#### Evaluation criteria for clinical efficacy of CHD angina pectoris

2.8.4

1.Main events: The incidence of cardiovascular events includes acute myocardial infarction, PCI or CABG.2.Secondary events(a)All causes of death.(b)Readmission due to cardiovascular events.(c)Seattle Angina Questionnaire (SAQ): The degree of pain in angina pectoris, the frequency and duration of acute paroxysmal angina pectoris, etc.(d)Routine admission examination: Carotid artery color Doppler ultrasound, cardiac color Doppler ultrasound, electrocardiogram, transcranial color Doppler ultrasound, chest radiograph, and other imaging examinations; Clinical biochemical tests such as troponin, brain natriuretic peptide, emergency 7 items, myocardial enzyme, D-dimer, coagulation four items, hematuria and stool routine, etc.3.Adverse events:(a)Produce toxic reactions (such as severe gastrointestinal reactions, gingival bleeding, etc).(b)Anaphylactic shock.(c)Liver and kidney function damage caused by TCM.

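### Comparing efficacy by drug treatment duration is open to immortal-time and reverse-causation bias if duration means use accrued after week 0 and events can end treatment

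*Protocol article*

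**What the plan says.** Item 6 of section 2.11.2 reads: "Stratified analysis: Compare the stratified curative effects by drug usage and drug treatment duration". It gives no time origin for duration, no cut-offs, no landmark and no time-updated handling.

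Other parts of the protocol article determine what that analysis would mean:

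- Exposure is observed, not assigned. Patients are "divided into exposed group and nonexposed group according to whether or not the patients with CHD angina pectoris were treated with Chinese patent medicine" (section 2, Method), and no length of treatment is set.
- The main efficacy criterion is an event outcome: "The incidence of cardiovascular events includes acute myocardial infarction, PCI or CABG" (section 2.8.4). Death ("All causes of death") and cardiovascular readmission are secondary events.
- Follow-up runs to week 48: "The follow-up time points were 0th, 4th, 12th, 24th, and 48th weeks" (section 2.7). Medication changes are among the things observed.
- Item 2 of section 2.11.2 computes a relative risk from counts. Item 5 adds Kaplan–Meier and Cox, but the stated purpose of Cox is narrow: "Cox regression analysis was used to process truncated data of cardiovascular events caused by missed visits".
- Earlier treatment may continue: "Patients with CHD angina pectoris can be treated with the original scheme before admission during the study period" (section 2.6).

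**The concern.** How long a patient takes a Chinese patent medicine during the study is known only after follow-up has begun. Suppose patients are sorted by the duration they finally reach and their events are then counted from week 0. Follow-up that determines stratum membership is then also follow-up in which events are counted.

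A patient who dies in week 6 cannot reach a stratum of 24 weeks or more. A patient whose infarction, revascularisation or readmission in week 6 leads to stopping or switching will not reach it either. Their events fall in the short stratum, and the long stratum loses part of its early events because of how it was formed.

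The result can be an apparent dose-response, with longer use going with fewer events, for a drug that has no effect. The stated objective is to compare short-, medium- and long-term effects, so a reader could easily take such a pattern as evidence of long-term benefit.

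**Working it through.** The document gives no figure for the duration-stratified analysis, so there is none to reproduce. The check asks what the analysis would show if the drug did nothing.

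**Inputs**

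- Risk over 48 weeks: R = 0.059, the value of P0 in section 2.3. That section gives no time frame, so reading it as a 48-week risk is an assumption.
- Constant hazard (assumption).
- Intended duration uniform over 0 to 48 weeks, split at week 24 (assumptions). Half the patients therefore intend at least 24 weeks: π = 0.5.
- c = share of events at which treatment stops. The document does not give it, so it runs from 0 to 1.

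**Formulas**

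Risk of an event before week 24: q = 1 − √(1 − 0.059) = 0.02995.

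A patient who intended at least 24 weeks drops into the short stratum if an event before week 24 ends treatment, which has probability cq. Hence:

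- long-stratum risk = (R − cq) / (1 − cq)
- short-stratum risk = [(1 − π)R + πcq] / [(1 − π) + πcq]

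**Example, c = 0.25**

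cq = 0.00749.

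- Long: (0.059 − 0.00749) / (1 − 0.00749) = 0.0519.
- Short, with π = 0.5: (0.059 + 0.00749) / (1 + 0.00749) = 0.0660.
- Relative risk: 0.0519 / 0.0660 = 0.79.

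**Results, no drug effect**

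| Share of events ending treatment (c) | Long | Short | RR, π = 0.5 | RR, π = 0.75 |
|---|---|---|---|---|
| 0 | 5.9% | 5.9% | 1.00 | 1.00 |
| 0.10 | 5.6% | 6.2% | 0.91 | 0.83 |
| 0.25 | 5.2% | 6.6% | 0.79 | 0.65 |
| 0.50 | 4.5% | 7.3% | 0.61 | 0.45 |
| 1 | 3.0% | 8.6% | 0.35 | 0.22 |

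The two risk columns are for π = 0.5. The last column supposes that half the patients intend the full 48 weeks and the rest are uniform, so π = 0.75. Simulation of both settings agrees with the formulas to within 0.002 on the relative risk. Using R = 0.072 (P1 in section 2.3) with π = 0.5 hardly changes the result: 0.79 at c = 0.25 and 0.35 at c = 1.

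**Would it reach significance?**

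Take the planned 6,200 exposed patients, c = 0.25 and π = 0.5, which gives about 3,077 long and 3,123 short.

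- Difference: 0.0660 − 0.0519 = 0.0141.
- Standard error: √[0.059 × 0.941 × (1/3,077 + 1/3,123)] = 0.0060.
- Expected z: about 2.36.

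A two-sided 0.05 test would reject about 65% of the time for an inert drug. At c = 0.10 the same calculation gives about 16%, and at c = 0 it gives 5%.

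**Comparator**

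In the simulations, a week-24 landmark (classify by treatment up to week 24, then count later events in patients still event-free) returned a relative risk between 0.99 and 1.01 throughout.

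**The case against.** The strongest reply is that the bias needs two conditions, and the document states neither.

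First, duration is not defined. Section 2.6 lets earlier treatment continue, so duration could mean use before week 0, which carries no immortal time. The short-, medium- and long-term objective could also mean comparing the two groups at successive visits, which sorts nobody by their future. This stands as a limit on certainty. On-study duration is still the natural reading, because no duration is assigned and treatment changes are followed to week 48.

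Second, a reader might infer that only patients who stay event-free can enter a long-duration stratum. The document does not support that. Infarction, PCI and CABG can be survived, and nothing says that treatment or follow-up ends when one occurs. The diagnostic criteria also accept patients with earlier events, for example "The definite history of old myocardial infarction". Only death strictly stops duration, and it is a secondary event. For the same reason, the document does not support saying that the analysis will show a dose-response, or that 0.35 is the expected size. That figure is the extreme at which every event ends treatment.

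Third, section 2.11.1 promises a statistical analysis plan with detailed steps, and that plan is not shown. It may define duration and handle it properly. But the protocol already names the stratifier, and taken literally the method can give a biased answer, so a correction there is worthwhile.

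Finally, drug usage in item 6 may simply mean the product or regimen recorded at entry, which raises no such problem.

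**Conclusion.** The point holds in conditional form. If duration is counted after week 0 and some deaths or events end treatment, item 6 is biased towards longer use. Under the stated assumptions with π = 0.5, the null relative risk lies between 1.00 and 0.35. The governing quantity is the share of events that end treatment, and the document does not give it. The intended-duration distribution also matters: the extreme falls to 0.22 if half the patients intend the full 48 weeks.

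The problem is confined to this stratified analysis. Membership of the exposed or nonexposed group does not depend on the duration finally reached, so the main comparison is untouched. That makes this a correction worth making before analysis, but not one on which the study's primary result depends.

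**What to change.** In item 6, state from what date duration is counted. For use accrued after week 0, replace stratification by final duration with one of these:

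- cumulative exposure to Chinese patent medicine as a time-updated covariate in the Cox model; or
- landmark analyses at weeks 4, 12 and 24 that classify patients by treatment up to the landmark and count only later events in patients still event-free.

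Keep plain strata only for characteristics fixed at week 0, such as the product in use and the prior duration of use.

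The cost is wording and programming. The landmark version also loses events before each landmark. Section 2.7 already observes medication changes at the visits and section 2.9 records when outcomes occur. The sponsor should confirm that the case report form captures start and stop dates for the Chinese patent medicine itself, since section 2.7 speaks of concomitant medication. Either method removes the sorting by future duration. Neither removes confounding when worsening angina leads a patient to stop before the event, so that limit should be stated with the results.

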#### Safety analysis

2.11.3

The safety analysis of each group of cases is mainly based on descriptive statistics, including the incidence rate of adverse events and abnormal changes in the specific description of adverse events and their relationship with drug administration.

#### Ethical principles

2.11.4

The subjects were voluntary subjects from 5 centers, all of whom independently signed informed consent forms and put them into CRF inserts. Ethical review prior to the start of clinical research, research on this topic must be reviewed by the ethics committee of each center's research unit. The subject has passed the ethical review by the ethics Committee of Tianjin University of TCM. The approval document number for the ethics review is TJUTCM-EC20190007. It was registered with the Chinese Clinical Trial Registry on July 14, 2019 with registration number ChiCTR-1900024532. Registered at the Clinical Trials.gov on July 16, 2019, registration number is NCT04022031.

## Discussion

3

The results of cohort study belong to Class II evidence-based medicine and have advantages such as long-term, large sample, and so on. In the prospective cohort study, we can directly obtain the 1st-hand data on exposure and outcome, so the bias of the data is small. On the basis of the National Basic Research Program of China (973 projects), this study has carried out a rigorous and meticulous design of this plan and has the following advantages:

1.Fully collect important clinical-related results and the main indicators, secondary indicators and adverse event reports included in the test.2.Strict concomitant medication regulations: As patients with CHD are often complicated with hypertension, hyperlipidemia, and other diseases, or undergo PCI surgery, they need to take antihypertensive, antiplatelet agglutination, and other drugs for a long period of time. This study has strict regulations on concomitant medication, reflecting the rigor of the design.3.Accurate methodology design to reduce the risk of bias: Before statistical analysis of clinical test data, statistical analysts shall formulate statistical analysis plans, specify detailed statistical analysis steps, and carefully check, clean up and confirm clinical test data.4.Strict quality control in clinical research: Due to different clinical units, to prevent the differences in the process of collecting samples, the research group dispatched uniformly trained supervision and inspection personnel to carry out off-site and on-site supervision and inspection work on clinical units to ensure the strictness of the patients enrolled. The filling of clinical scales is also carried out after training, and professional personnel supervise and verify the data on site. The later research group uniformly conducts 2 rounds of verification on the data to ensure the accuracy of the original data.5.Unified sample collection and testing: Collected blood and urine samples are collected, transported, processed, and stored in a unified way. Biochemical indexes, liquid chips, and expression spectrum chips are all detected by professional companies to ensure the unity of the detection process.

Due to the complexity of clinical research, although the research scheme has strict regulations on possible problems, it may still affect some research results. The clinical research plan of this kind of research will be further improved in the later period according to the actual research situation. This plan will comprehensively explore the clinical efficacy advantages of Chinese patent medicine in adjuvant treatment of CHD angina pectoris, and provide reliable data support for its clinical application.
